## Abstract

**Background:**

Adjustment disorder is one of the most common mental health diagnoses. Still it receives relatively little attention from researchers trying to establish best interventions to treat it. With high prevalence of stressful life events, which might be leading to adjustment disorder, and limited resources of mental health service providers, online interventions could be a very practical way of helping people who have these disorders or are in the risk to develop them. The proposed study protocol is aimed to describe a randomized controlled trial of an internet-based modular intervention for adjustment disorder as it is defined in a proposal for the ICD-11.

**Methods/design:**

This study is a two-armed Randomized Controlled Trial (RCT) to examine the effectiveness of a web-based intervention BADI (Brief Adjustment Disorder Intervention) for adjustment disorder symptoms. BADI has four modules: Relaxation, Time management, Mindfulness and Strengthening relationships. It is based on stress and coping research and integrates evidence-based treatment approaches such as Cognitive Behavioural therapy (CBT), mindfulness and body-mind practices, as well as exercises for enhancing social support. Primary outcome of the study are symptoms of adjustment disorder and well-being. Engagement into the program and motivation for change is a secondary outcome. All participants after completing the baseline assessment are randomly assigned to one of the two groups: either to the one in which participant will instantly gain access to the BADI intervention or a group in which participants will be given access to the BADI program after waiting one month. Participants of BADI can choose exercises of the program flexibly. There is no particular order in which the exercises should be completed.

**Discussion:**

Study will provide new insights of modular internet-based interventions efficacy for adjustment disorders. The study will also provide information about the role of motivation and expectancies on engagement in modular internet-based interventions. In case this RCT supports effectiveness of fully automated version of BADI, it could be used very broadly. It could become a cost-effective and accessible intervention for adjustment disorder.

**Trial registration:**

The study was retrospectively registered with the Australian and New Zealand Clinical Trials Registry with the registration number ACTRN12616000883415. Registered 5 July, 2016.

## Background

### The new concept of adjustment disorder

Adjustment disorder is one of the most common mental health diagnoses around the world [1]. Despite that, it has been considered a poorly defined area of psychopathology, therefore conceptual changes were proposed both for DSM-5 and ICD-11 [2–5].

In DSM-5 adjustment disorders have been classified under trauma and stress related disorders for the first time. However, some scholars argue that they still remain rather loosely defined [5]. Proposals for ICD-11 conceptualize adjustment disorder as a maladaptive reaction to identifiable stressors [4]. Intrusive preoccupations with the stressor, avoidance and failure to adapt should separate this disorder from normal reactions and no requirements for severity of the stressor should distinguish it from PTSD [3, 4, 6].

This new conception of adjustment disorder, that was proposed for ICD-11, was employed in a representative national wide survey of general population in Germany [2]. Results of the study indicated 0.9 % prevalence of adjustment disorder fulfilling clinically significant impairment criterion, and 1.4 % without fulfilling this criterion. This study also established life events that were most frequently associated with adjustment disorder: serious illness, conflict with neighbours and job-related conflict. The proposed new structure of the adjustment disorder was also recently validated in a Lithuanian representative population sample [7]. This study supported the two core symptom adjustment disorder structure.

### Interventions for Adjustment disorder

In addition to vagueness of definitions, adjustment disorder received relatively little attention from researchers trying to establish best interventions to treat it [5, 8]. As evidence for the benefits of pharmacological treatment is extremely limited, psychotherapeutic interventions are considered as treatment of choice [5, 8, 9]. Among specific psychotherapeutic approaches the following were tried without clear consensus which are the most effective: supportive, psychoeducational, cognitive, psychodynamic, Interpersonal, ego-enhancing, problem-solving, eye movement desensitization and reprocessing, support groups, “mirror psychotherapy” and “activating intervention” [5, 8, 9].

### E-health advantages in treating adjustment disorder

Having in mind high prevalence of stressful life events, which might be leading to adjustment disorder, and limited resources of mental health service providers, online interventions could be a very practical way of helping people who have these disorders or are in the risk of developing them. Especially if these interventions could be provided automatically, thus requiring little human resources.

Studies of another more severe stress related disorder – posttraumatic stress disorder (PTSD) – show that stigmatization of help, practical issues such as incompatible time, transportation problems, financial problems, lack of professional services in residential area, negative prejudice about the effectiveness and availability of help are among those barriers that prevent people from getting help they really need [10, 11]. Internet-based interventions might be a good way to remove at least some of these obstacles for treatment.

A meta-analysis of the effectiveness of internet-based psychotherapeutic interventions for various conditions showed that these interventions could be as effective as face to face therapies [12]. A more recent meta-analysis of telehealth treatments supported the use of telehealth treatments specifically for individuals with PTSD-related symptoms [10]. To our knowledge there are only two telehealth interventions developed specifically for adjustment disorders [8]. Both interventions have not been evaluated in large-scale empirical studies yet.

We have developed a web-based intervention BADI (Brief Adjustment Disorder Intervention) to help people to deal with adjustment disorder symptoms after stressful life events. This paper reports on the protocol of a RCT examining the effectiveness of this intervention.

### Aims of the study

There are two aims of this RCT: 1) to evaluate the effectiveness of an internet-based modular intervention for adjustment disorder (BADI); 2) to examine correlations between effectiveness, motivation, expectations, drop-out and adherence.

## Methods/design

BADI is an open access internet-based modular intervention for adjustment disorders registered with the Australian and New Zealand Clinical Trials Registry with the registration number ACTRN12616000883415. The study was considered and approved by Vilnius University Psychology Research Ethics Committee. This study follows CONSORT E-HEALTH guidelines [13]. Figure 1 represents procedure of the study schematically.

**Fig. 1 Fig1:**
[figure not shown]
Flow chart of the study

### Setting

Participation in the study is online only. Vilnius University is the administering institution of the study website.

### BADI intervention

BADI program is a structured short-term online intervention program addressed to people with adjustment disorders or those who are experiencing stressful life events and have a risk for adjustment disorders. BADI program is focused upon enhancing process of psychological resilience, utilizing personal and social resources and developing better coping skills.

The program consists of four modules: Relaxation (named “Body”), Time management (named “Time”), Mindfulness (named “Space”) and Strengthening relationships (named “Relationships”). Descriptions of exercises are provided in Table 1.

**Table 1 Tab1:** BADI content

*Module*	*Exercise*	*Aim of the exercise*	*Activity in the module*
Relaxation “*Body”*	Progressive muscle relaxation	Relieving muscle tension, relaxing body, enhancing stress resistance. Learning how to actively relax in stressful situations	Progressive relaxation using voice-guided instructions. Participant performs progressive muscle relaxation exercise. Duration 5-10 min.
	Breathing awareness	Recognising breathing pattern and relaxing	Structured self-observation exercise. Participant concentrates on breathing and present moment. Duration 5-10 min.
	Body scanning	Focusing mindful attention, reducing tension, achieving mind-body balance	Voice-guided structured exercise. Participant focuses on breathing and sensations. Duration 5-10 min.
Time management “*Time”*	Priorities of the day	Recognising core values, choosing between alternatives, establishing personal guidelines	Voice-guided fantasy exercise and pencil-paper list making. Participant plans and implements important day activities. Duration 5-15 min.
	Accomplishment	Revealing valuable task of the day, planning action and execution	Participant writes down three tasks, then chooses one and divides it into smaller pieces. The participant then makes a schedule for those divided taskas. Duration 5-10 min.
	Planning pleasant activities	Making decisions, taking actions, preventing distress, creating positive experiences	Brainstorming, planning and implementing homework assignment. Participant plans and implements pleasant activity. Duration 5-10 min.
Mindfulness “*Space*”	Walking meditation	Establishing posture, concentrating on action, relaxing and focusing attention	Voice-guided structured exercise. Participant performs relaxation and meditation while walking. Duration 5-10 min.
	Seeing meditation	Anchoring attention, relaxing and concentrating on the moment	Voice-guided structured exercise. Participant performs sight concentration exercise focusing attention at the moment. Duration 5-10 min.
	Letting go of thoughts	Concentrating on sensations, relieving negative thoughts and tension	Voice-guided structured exercise. Participant performs visualisation exercise. Duration 5-10 min.
Strengthening relationships “*Relationships*”	Partners’ encouragement	Developing empathy, sharing partners’ feelings, coping with interpersonal stress and preventing conflict	Reflexion, structured action planning and implementation exercise. Participant is asked to choose one way to encourage partner and realise this at the moment. Duration 10-15 min.
	Assertive message	Sharing expectations, training assertiveness, preventing conflict and increasing social support	Reflexion, structured action planning and implementation exercise. Participant reflects upon important people and shares assertive message to them. Duration 5-15 min.
	Appreciation	Expressing appreciation, encouraging cooperation, strengthening connection	Reflexion, structured action planning and implementation exercise. Participant shares ones needs and appreciation with the partner. Duration 5-10 min.

BADI program is based on stress and coping research and integrates evidence-based modern treatment approaches such as Cognitive Behavioural therapy (CBT), mindfulness and body-mind practices, as well as exercises for enhancing social support.

Relaxation module exercises were selected considering research on the topic. Progressive muscle relaxation effectiveness studies demonstrated that it could be a useful technique in various fields of medicine [14–16]. BADI relaxation module also includes breath and body scanning exercises which are based on combined body and mindfulness principles [17–20].

The focus of Time management module is to stimulate problem-focused stress coping [21]. The analysis of coping strategies revealed that problem-focused coping is more efficient than emotion-focused [22] and is related to greater health benefits and better adjustment.

BADI mindfulness module is based on a review of rapidly growing evidence of effect of mindfulness on stress and well-being (e.g. [23–26]).

Social support is another important part of effective coping with stress [27]. BADI relationships module includes partner encouragement exercise, assertive message and appreciation which enhance stress coping through open communication and social support [18, 21].

Exercises take from 5 to 15 min to complete. The participant may complete as many or as few modules as they choose. This enables a participant to personalize the intervention to his needs. The participants are instructed that they will have access to BADI for one month.

### Participants

#### Inclusion criteria

All individuals willing to participate in the study have to have adjustment difficulties and be no less than of 18 years old, have access to internet and a computer or a smart gadget with screen and audio output, and also have sufficient Lithuanian language literacy to understand the instructions and give informed consent.

#### Exclusion criteria

Risk of suicide, severe adjustment difficulties.

#### Withdrawal criteria

Individuals who wish to terminate their participation in the program are asked if they would consent to completing following assessments. If not, no further remainder e-mails or invitations to complete assessments are sent.

#### Recruitment

All participants are self-referred. Study is advertised via social media and media, and can be accessed via Facebook links, and media articles.

#### Enrolment

Participants interested in the study can register to the program at the intervention website. Eligible participants are then provided with detailed information about the study and are asked to give an informed consent. After giving informed consent and filling in the self-report measures of the initial assessment (T1) they are asked to wait until they are approved for the participation.

#### Randomization

The randomization process is continuous in a way that the participant is instantly allocated to the intervention or waiting-list control group within 24 h of completing the initial assessment. Randomization is conducted by study team member using an online true random number service www.random.org. Participants are randomized in 1:1 ratio to study groups. No stratification is applied.

#### Blinding

Participants are not blinded to possible groups. Participants are informed that after completing the baseline assessment they would be randomly assigned to one of the two groups: either to the one in which participant will instantly gain access to the BADI intervention or a group in which participants will be given access to the BADI program after waiting for one month.

### Study groups

#### Intervention BADI

Participants in the intervention BADI group have full access to the intervention modules for 30 days. Participants can freely select any of the BADI intervention exercises. Participants can complete as many or as little exercises as they need. Participants can do exercises in any order they prefer. There are no instructions to complete all exercises. Participants can choose to complete one or more exercises and do them repeatedly. Weekly remainder e-mails are sent once per week to participants. Participants are reminded that for stress management skills to improve they need to use the intervention as frequently as possible.

#### Waiting-list control

Participants in the waiting-list control group are asked to continue with their everyday life and come back for a secondary assessment after 30 days, after completing the secondary assessment they receive access to the intervention for one month.

### Outcomes

Self-report questionnaires are used for assessment of primary outcomes.

#### Primary outcomes

The main outcome measures are psychological well-being and severity of Adjustment disorder symptoms. Level of adjustment disorder symptom severity is evaluated with Adjustment disorder new model (ADNM-20) [28] questionnaire. This questionnaire is constructed of a stressors list and evaluation of symptoms. The list is composed of seven of acute events (e.g. divorce, moving) and nine chronic stressors (e.g. conflict with neighbours, serious illness). Participants are instructed to indicate all severe events from the list that they had experienced in the last 2 years and that caused significant level of stress. There is also a blank item for participants to fill in other significant stressors. Psychometric properties of the Lithuanian version of the ADNM-20 questionnaire are acceptable [7].

The WHO-5 Well-being Index (WHO-5) [29] is a short self-report measure for well- being assessment. Participants are asked to rate how each of the 5 statements applies to them when considering the last 2 weeks. Each item is scored from 5 (all of the time) to 0 (none of the time). The raw score therefore ranges from 0 (absence of well-being) to 25 (highest well-being). Participants who score > 16 on ADNM and < 50 on WHO-5 are included into the study.

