In case this RCT supports effectiveness of a fully automated version of BADI, it could be used very broadly. BADI could become a very cost-effective and accessible intervention for adjustment disorder.

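### Entry does not require an endorsed stressor, so a result in this sample does not by itself support a conclusion about adjustment disorder as the ICD-11 proposal defines it

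*Protocol article*

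**What the plan says.** **The condition.** The Abstract (Background) describes an "internet-based modular intervention for adjustment disorder as it is defined in a proposal for the ICD-11". The section on the new concept of adjustment disorder gives the definition: "Proposals for ICD-11 conceptualize adjustment disorder as a maladaptive reaction to identifiable stressors". It adds: "Intrusive preoccupations with the stressor, avoidance and failure to adapt should separate this disorder from normal reactions".

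**The wider target.** The section on the BADI intervention also addresses the programme to "those who are experiencing stressful life events and have a risk for adjustment disorders". The section on e-health advantages likewise describes BADI as help with symptoms that follow stressful events.

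**Who may enter.** Inclusion criteria: "All individuals willing to participate in the study have to have adjustment difficulties and be no less than of 18 years old". The other inclusion conditions are practical ones (internet access, a device, Lithuanian literacy). Exclusion criteria: "Risk of suicide, severe adjustment difficulties". The numerical rule stands under Primary outcomes: "Participants who score > 16 on ADNM and < 50 on WHO-5 are included into the study".

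**What is recorded.** Primary outcomes describes the ADNM-20 as a stressor list (seven acute events, nine chronic stressors and a blank item, over the last two years) plus a symptom evaluation.

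**The hoped-for conclusion.** If the trial supports the automated version, "BADI could become a very cost-effective and accessible intervention for adjustment disorder" (Discussion).

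**The concern.** The narrow definition and the broader at-risk target share one element: a stressor. The entry rule leaves it out. As written, a self-referred adult with raised symptom scores and no indicated event is not ruled out. Such a person belongs neither to the group with the disorder nor to the at-risk group that the article describes.

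What is at stake is whom the result describes. If the sample includes people whose distress has another origin, a positive result may come partly from them, and a null result may partly reflect them. Without a stressor condition or a classification at baseline, a reader cannot separate these possibilities, and the step to a conclusion about adjustment disorder is not secured.

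**Working it through.** **1. Is a stressor part of the stated population, and is it required for entry?**

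| Place in the protocol article | Stressor |
|---|---|
| Abstract (Background), with the definition in the new-concept section | Part of the condition |
| E-health advantages | Part of the purpose |
| BADI intervention, at-risk group | Part of the target |
| Inclusion criteria | Not mentioned; adjustment difficulties left undefined |
| Exclusion criteria | Not mentioned |
| Primary outcomes, entry rule | Not mentioned; two scores only |
| Primary outcomes, ADNM-20 description | Recorded, but not tied to entry |

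Every description of the population presupposes a stressor, and no entry condition requires one.

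**2. Is the information available in time?** Under Enrolment, the self-report measures of T1 are completed before approval. Under Randomization, allocation follows within 24 hours of the initial assessment. The ADNM score decides entry and the primary analysis runs from T1 to T2, so the ADNM-20 is in hand at T1.

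**3. What do the two cut-offs select?**
- WHO-5: five items scored 0 to 5 give a raw range of 0 to 25. All 26 possible scores are below 50, so the printed cut-off excludes nobody. On a percentage scale (raw × 4, an assumption) it means a raw score of 12 or below, since 12 × 4 = 48 and 13 × 4 = 52.
- The Sample size section also points to a scale other than the one described. It gives a difference of 10, 73 per arm, 80 % power and α = .05, but no SD, so 73 cannot be reproduced directly. Solving for the SD, two-sided: 10 × √(73/2) / (1.960 + 0.842) = 21.6; one-sided, 24.3. The largest possible SD on a 0-25 scale is 12.5. The calculation therefore cannot be on the raw score.
- ADNM: the article gives neither the score range nor whether the cut-off of 16 applies to a total or to a core-symptom score. If it is a total of 20 items scored 1 to 4 (assumption), the minimum is 20 and everyone passes. If the items are scored 0 to 3 (assumption), entry needs at least 17 of 60.

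**4. Can a dilution be calculated?** Let f be the share of entrants who meet the definition, with mean effect A, and let the rest have mean effect B. The whole-sample effect is f·A + (1 − f)·B. The documents give none of f, A and B separately. Illustration only, with A = 10, SD 21.56, 73 per arm and a two-sided test:
- B = 10: no dilution, and power stays at 80 % for any f.
- B = 0: power is 71 % if the rest make up 10 % of the sample, 61 % at 20 %, 50 % at 30 % and 29 % at 50 %.

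The range runs from no loss to a large one, and nothing in the article places the trial within it.

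**The case against.** The strongest reply is that the trial does what it sets out to do. The Abstract (Methods/design) words its purpose as effectiveness for adjustment disorder symptoms, the primary outcome is symptom severity, and people at risk are included on purpose. Randomisation protects the contrast among whoever enrols, and natural recovery over the 30 days is expected in both arms. All of this stands. A reader might infer that the trial cannot answer its question; the documents do not support that.

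A reader might also infer that the core symptoms play no part in entry. That is not established either, since the article does not say which ADNM score the cut-off of 16 refers to.

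Third, the ADNM-20 contains a stressor list, the inclusion criterion on adjustment difficulties may be applied with a stressor in mind, and there is an approval step after T1. Since this is a condensed article, a stressor check might sit in the full protocol. That is possible, but the entry rule is printed as an operative rule with two numbers, and no stressor condition is among them.

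Finally, the Discussion is worded conditionally. The condition, however, is that the trial supports effectiveness; it does not concern whether the sample has the disorder.

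The at-risk argument does not remove the mismatch, because the at-risk group is itself described by stressful events.

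**Conclusion.** The point holds as a mismatch between the stated population and the entry rule. The between-arm comparison is valid for the people enrolled. What is not supported by the entry rule alone is a conclusion about adjustment disorder as the ICD-11 proposal defines it, which is how the Abstract (Background), the Aims and the Discussion frame the trial.

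No size can be put on the consequence. A reader might take a figure for lost effect or lost power from the zero-effect illustration, but it assumes both the share and the absence of benefit in the rest, and the programme is also aimed at people at risk. Nor does the 0.9-1.4 % prevalence quoted in the background settle the share: it describes an unselected general population, not self-referred adults screened on symptoms.

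The scale problem is firmer: on the WHO-5 score that the article describes, the cut-off of 50 has no effect. How selective the ADNM cut-off is cannot be judged from the text.

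The verdict assumes that the printed entry conditions are complete. If a stressor check already operates at approval, it need only be stated, and the remaining points are the baseline classification, the wording and the scales.

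**What to change.** 1. **Entry rule.** Under Inclusion criteria and Primary outcomes, add that at least one event on the ADNM-20 stressor list, or an entry in its blank item, must be indicated at T1.
2. **Baseline classification.** Classify each randomised participant from the T1 ADNM-20 as meeting or not meeting the core-symptom definition, by a rule stated in advance. Report the T1-T2 group contrast in those who meet it as a supportive result beside the whole-sample primary analysis.
3. **Wording.** State the aim and conclusion as adjustment disorder symptoms in self-referred adults with, or at risk of, adjustment disorder, unless the subset supports more.
4. **Scales.** In the sentence that gives the entry rule, state the scale of both cut-offs and which ADNM score is meant, and reconcile the WHO-5 cut-off with the 0-25 range given just before it.

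**Cost.** One line in the eligibility check and one extra analysis, on data already collected. A few registrants become ineligible, and the subset estimate is less precise than the whole-sample one. Registration was retrospective, so enrolment may have begun. For participants already enrolled, only the classification, the subset report and the wording changes apply.
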